### Data monitoring

As the intervention(s) provided in the present trial poses little or no risk to the participating patients, no data monitoring committee will be composed. Funding sources of the current trial has no part in the design, conduction or reporting of the trial, thus there is no conflict of interests. As the intervention(s) poses little or no risk to the participating patients no interim analyses will be applied. Stopping guidelines for discontinuing and modifying the exercise has been described previously (see the “Criteria for modifying and discontinuing” section).

### Access to the final trial dataset

The principal investigator and principal supervisor will have full access to the dataset as well as all co-authors. A fully patient-anonymized dataset and corresponding statistical analysis code will be made available for the scientific journal reviewing the manuscript and its results within 6 months in line with the recent proposal from the International Committee of Medical Journal Editors (ICMJE) [52].

### Ancillary and post-trial care

The current trial is not planned to include patient ancillary care or post-trial care. On completion of the trial, if participants want to continue with the exercises independently they can do so. However, this will not be a part of the trial and will be on the patient’s own initiative.

### Dissemination policy

The QUADX-1 trial is planned to be reported in three manuscripts, which will be published in scientific peer-reviewed journals. All manuscripts will refer to the QUADX-1 trial’s Clinical.Trials.gov identifier. The first manuscript will be the trial protocol, the second manuscript will be the primary trial report of the investigated dose-response relationship, and the third manuscript will be a qualitative study investigating enablers and barriers for patient adherence to home-based exercise and physiotherapists’ experience in administering home-based exercise before TKA. The results will also be presented at relevant scientific conferences and symposiums. Trial participants will be informed of the trial via a letter explaining the results in layman’s terms. On request, the data underlying the results presented in the manuscript will be available to reproduce the findings. We intend to make the dataset – containing de-identified individual patient data – publicly available no later than 6 months after publication, consistent with the recent proposal from the International Committee of Medical Journal Editors (ICMJE) [52], if it complies with national regulations, e.g., the Danish Data Protection Agency. Trial data can be requested by contacting the main investigator ([name]) or trial director (TB). Positive as well as negative and inconclusive results will be published.

All contributors to the study will be offered to co-author the three above manuscripts if they fulfill the International Committee of Medical Journal Editors (ICMJE) recommendations for authorship [52]. No professional writers will be used.

## Discussion

In 2011, approximately 60,000 patients were registered in the Danish health care system with symptoms of knee OA and the annual incidence of knee OA has increased from 35.8 in 1997 to 155.2 in 2010 per 100,000 inhabitants [3]. Consequently, this population is very large and growing, which stresses the importance of optimizing the treatment offered to these patients. The *QUADX-1 trial* will add knowledge relating to which knee-extensor strength exercise dosage is most effective in increasing knee-extensor strength and whether a single, home-based (unsupervised) knee-extensor strength exercise is feasible in patients with end-stage knee OA.

The minimal treatment approach (single exercise) has been chosen as it is a pragmatic and time-saving solution [46]. Further, the rationale for investigating a home-based, single knee-extensor strength exercise is that it could improve exercise adherence as it is simple (minimal intellectual effort), does not take a long time (requires less surplus energy) and is likely to inflict less pain (less stress imposed on the knee joint). An exercise targeting the knee-extensor muscle is chosen as it is the single most important muscle for function in the knee OA population [9, 10, 13, 14].

In summary, the objective of the *QUADX-1 trial* is to investigate the efficacy of three different exercise dosages of pre-operative, home-based, knee-extensor strength exercise before and shortly after surgery in patients eligible for total knee replacement. The results will indicate which knee-extensor strength exercise dosage is most effective for increasing knee-extensor strength in the end-stage knee OA population. Furthermore, the results will indicate whether pre-operative knee-extensor strength exercise improves knee-extensor strength and function prior to surgery and whether this effect (if any) is sustained following surgery.

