## Background

Patients diagnosed with knee osteoarthritis (OA) report pain, low quality of life and limitation in physical activities [1]. As a consequence, in Denmark, around 8000 patients with end-stage knee OA receive surgical treatment annually, in the form of total knee arthroplasty (TKA), to overcome their knee-related disabilities [2]. Currently, the two primary treatments for knee OA are non-surgical treatment (e.g., pain treatment, exercise and weight loss if indicated) and surgery (TKA) [3].

There is preliminary evidence that pre-operative exercise may postpone total hip arthroplasty in patients with hip OA [4]. Likewise, pre-operative exercise in candidates for TKA will provide an optimized basis for deciding whether to commence TKA; e.g., patients experiencing pain relief and functional improvement following exercise might benefit from postponing their potential TKA and vice versa. The latest systematic review on the efficacy of pre-operative strength exercise to enhance post-operative recovery after TKA and THA concludes that pre-habilitation may slightly improve early post-operative pain and function among patients undergoing total joint replacement; but the effects are too small and short-lived to be considered clinically important [5]. However, this conclusion is based on trials with significant limitations, providing very low certainty in estimates [5].

Recently, the first randomized controlled trial investigating the efficacy of TKA in patients eligible for TKA was conducted [6]. It showed an added effect (pain relief and functional improvement) of 30% by TKA and non-surgical treatment to that achieved by non-surgical treatment alone (30%). This highlights the importance of coordinating non-surgical and surgical care to select the right candidates for surgery, especially as patients undergoing TKA seem to experience more serious adverse events compared to non-surgical treatment [6]. These results suggest that non-surgical treatment should at least be tried out and considered before commencing surgical procedures. Optimally, patients awaiting TKA would conduct home-based, pre-operative exercise as the effect of exercise helps to establish the potential need for a future orthopedic operation. At the same time, it would be a potential solution of little cost and it enables the patients to self-manage their symptoms.

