### Outcomes

The trial is designed with four pre-determined outcome assessments; at baseline (week 0) (t_0_), after 12 weeks of home-based exercise (2–8 days after the final exercise session), corresponding to the endpoint before surgery (t_1_), at hospital discharge 1–8 days after surgery (t_2_) (provided surgery is performed) and finally, 3 months after surgery (t_3_) (Fig. 2) (provided surgery is performed). The primary endpoint is after the intervention period (t_1_). Secondary endpoints of interest are just before hospital discharge 1–8 days after surgery (t_2_) and 3 months after surgery (t_3_).

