### Sample size

For a three-group-level One-way ANOVA of a normal mean difference with a two-sided significance level of 0.05, a common standard deviation of 0.22 Nm/kg (isometric knee-extensor strength measurement) [51], and a minimal clinically important difference of 0.15 Nm/kg (15%), a sample size of 126 (42 per group) patients is required to obtain a power of 80%. To allow for a dropout rate of 10%, we will include 140 patients in total for the intention-to-treat (ITT) analysis (3 × 42 + 14 = 140).

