#### Secondary analyses

The secondary analyses will be between-group contrasts for the secondary outcomes at the primary and secondary endpoints. Figure 7 illustrates a hypothetical presentation of changes in isometric knee-extensor strength for the three groups during the whole trial period.

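### The planned tables give no pre-surgery (t0–t1) result for the operated patients, so a statement that the dosage effect is or is not sustained after surgery can reflect who was measured

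*Protocol article*

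**What the plan says.** **Who is measured when.** The Trial design section places t1, the primary endpoint, after the exercise period and before any surgery, for all randomised patients. The Outcomes section places the next assessment "at hospital discharge 1–8 days after surgery (t_2_) (provided surgery is performed", and attaches the same condition to t3. Under Secondary analyses, patients who decline surgery move to annual assessments in a separate small case study, so they have no counterpart to t2 or t3.

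**How surgery is decided.** The Abstract and Recruitment sections say the need for surgery is re-assessed after the 12 weeks of randomised exercise. The Background says that "patients experiencing pain relief and functional improvement following exercise might benefit from postponing their potential TKA". Row 9 of Table 3 hypothesises that need for surgery, as the patient states it at t1, differs between dosage groups.

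**What is planned and promised.** Tables 3 and 4 list strength contrasts for t0–t1, t0–t2 and t0–t3 by arm. The Secondary analyses section adds that "Figure 7 illustrates a hypothetical presentation of changes in isometric knee-extensor strength for the three groups during the whole trial period". The Missing data section applies intention to treat with multiple imputation to all analyses. The closing summary of the Discussion says the results will indicate "whether this effect (if any) is sustained following surgery".

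**The concern.** Whether an effect is sustained is a statement about the same people at two times. Here the t1 contrast describes everyone randomised, while the observed t2 and t3 contrasts describe those who went on to surgery. Membership of the second group is settled after randomisation, and the protocol anticipates that it may be related to response and to arm. A contrast present at t1 could shrink, vanish or appear at t2/t3 with no change in any individual patient's dosage effect. A reader given Table 4 as laid out could not tell this from true loss or persistence.

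The outcome after surgery is part of the trial's stated purpose, so this is not incidental. The Limitations section mentions the lack of a control group, the selection of motivated volunteers and possible bias in the need-for-surgery answer, but not this change of population.

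**Working it through.** **Inputs from the protocol (Sample size section).** "a common standard deviation of 0.22 Nm/kg"; target difference 0.15 Nm/kg; 42 per group (126 in all) for 80% power; 10% dropout.

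**The plan's own figure.** One-way ANOVA, three groups, alpha 0.05, means 0, 0.075 and 0.15. Noncentrality = 42 × (0.075² + 0 + 0.075²)/0.22² = 42 × 0.01125/0.0484 = 9.76. Power is 79.5%, and 43 per arm first reaches 80%. Dropout: 126/0.9 = 140. The stated figures are reproduced to within one patient per arm. They concern t1 in all patients.

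**Inputs not in the protocol (assumed).** The 0.22 is taken as the SD of the t0–t1 change; the protocol gives it for the strength measurement. The opt-out fraction p is 10% to 40%. The correlation ρ between strength gain and the tendency to opt out is 0.2 to 0.5.

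**Shift in the operated patients.** Suppose gain and a latent tendency to opt out are bivariate normal, and a patient opts out above the threshold z with P(Z > z) = p. The mean gain of operated patients then differs from that of all patients by −ρ × 0.22 × φ(z)/(1 − p).

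| p | z | φ(z) | 0.22 × φ(z)/(1 − p) | ρ = 0.2 | ρ = 0.3 | ρ = 0.5 |
|---|---|---|---|---|---|---|
| 0.10 | 1.282 | 0.1755 | 0.0429 | −0.009 | −0.013 | −0.021 |
| 0.30 | 0.524 | 0.3477 | 0.1093 | −0.022 | −0.033 | −0.055 |
| 0.40 | 0.253 | 0.3863 | 0.1417 | −0.028 | −0.043 | −0.071 |

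**Shift in the between-arm contrast.** With p = 0.10 in one arm and 0.40 in another, the shift is ρ × (0.1417 − 0.0429) = ρ × 0.0988. This gives 0.020, 0.030 and 0.049 Nm/kg for ρ = 0.2, 0.3 and 0.5, or 13%, 20% and 33% of 0.15. The sign depends on which arm has more opt-outs. With equal p and ρ in both arms, or with ρ = 0, the shift is zero.

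**Set against sampling error.** With 42 evaluable per arm, the operated numbers are 42 × 0.9 = 37.8 and 42 × 0.6 = 25.2. The standard error of the contrast is 0.22 × √(1/37.8 + 1/25.2) = 0.057, so 0.030 is about half a standard error.

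**Second illustration, by simulation.** Two arms (groups 2 and 4) have a true contrast of 0.15 that every patient fully retains. One common rule lowers the odds of surgery by a factor exp(b) per SD of strength gain. The contrast among operated patients is:

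| Operated overall | b = 0.5 | b = 1 | b = 2 |
|---|---|---|---|
| 90% | 0.147 | 0.140 | 0.127 |
| 70% | 0.143 | 0.129 | 0.106 |
| 50% | 0.142 | 0.124 | 0.095 |
| 30% | 0.143 | 0.124 | 0.090 |

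At b = 0 it stays at 0.15. Conversely, with no true effect at t2 and the same three values of b, operation rates of 70% v 50% give a spurious contrast of 0.021 to 0.051. Rates of 80% v 40% give 0.042 to 0.103. Either can go in either direction. The extremes need b = 2, an odds ratio of exp(−2) = 0.14 per SD, which is strong selection.

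**The case against.** Several points on the other side stand in part.

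- **No rule compares the contrasts.** A reader might infer that the plan judges persistence by testing t0–t1 in everyone against t0–t2/t3 in operated patients. No section says so. The contrasts are listed separately, and the promise is one sentence in the Discussion. That limits the charge, but the tables as laid out supply nothing else on which to base the promised statement.
- **Imputation puts everyone in.** Taken literally, the Missing data section brings all 140 patients into the t2/t3 analyses, so it cannot be said that these will be confined to operated patients. If the imputation model contained t1 strength, it could adjust for selection on measured t1 gain. The result would then be a hypothetical contrast, as if everyone had been operated on, extrapolated from those who were. A never-operated patient has no strength at discharge or at 3 months after surgery to recover.
- **Poorer responders.** It is tempting to conclude that the operated patients will be the poorer responders. The Background says only that improvers might benefit from postponing, and it speaks of pain and function, not strength. Row 9 of Table 3 concerns the patient's stated need, not operations performed.
- **Figure 7.** It is described as hypothetical and is not in the text at hand, so nothing here rests on which patients it would show.
- **Table 4 is a shell.** Extra rows are not excluded, and a full protocol or analysis plan could add them. The point is that the published layout and the published promise do not fit together.
- **The remedy is partial.** Restricting t1 to operated patients aligns the people compared but does not restore randomised comparability. If surgery follows measured t1 gain, measurement error (between-evaluator SEM 8.34–9.92% in the protocol) would also bring some regression to the mean between t1 and t2.

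**Conclusion.** The concern holds in a limited form. The plan promises a statement on persistence after surgery, but provides no result that follows the same patients from before to after it. A difference between the t1 and t2/t3 dosage contrasts can therefore come from who was measured.

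Under the assumed SD of change, opt-out of 10% v 40% and correlation of 0.2 to 0.5, the shift is about 0.02 to 0.05 Nm/kg. It is zero if surgery is unrelated to strength response. Neither the operation rates nor that correlation is in the document, so size and direction remain open. The document supports saying that the comparison can mislead, not that it will, nor in which direction. Only the secondary conclusions after surgery are touched; the t1 primary analysis is not. The change should be made, as it costs little and protects a stated aim of the trial.

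**What to change.** 1. In Table 4, add for each arm the number operated, and the t0 mean, t1 mean and t0–t1 contrast in operated patients.
2. Base any statement that an effect is or is not sustained on t1 against t2/t3 within these same patients, using observed values.
3. Label that comparison as conditional on surgery and not a randomised comparison, and note possible regression to the mean.
4. Keep the all-patient t0–t1 contrast as the primary result.

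Cost: a few table rows from data already being collected, no new visits, and a more cautious secondary conclusion.

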### Strengths

The trial design has several strengths as it addresses numerous gaps in the academic literature. Trials investigating the dose-response relationship of strength exercise in patients with end-stage knee OA are rare. Accordingly, there is a need for investigating the most effective exercise dose in this patient population, as highlighted in two recent systematic reviews using meta-analysis [21, 22]. Peer et al. highlight the scarcity of evidence related to exercise dose-response in patients with knee OA needed to guide pre-habilitation in clinical practice [22]. Further, Bartholdy et al. suggest that a 30–40% gain in knee-extensor strength is needed to positively affect pain and disability in patients with knee OA [21], highlighting the need for evidence to suggest the exercise dosage required to obtain adequate improvement in knee-extensor strength.

Adherence to home-based exercise is reported to be low with a high risk of over-reporting [45–48]. The use of sensors attached to the elastic exercise band will address this in an objective manner. Further, in a recent systematic review on adherence with physiotherapy exercises it was requested that the relationship between adherence and treatment outcome was investigated [46].

The exercise regimes currently offered to patients with knee OA are mostly supervised exercise sessions at outpatient clinics and comprise several exercises resulting in accumulated time spent and cost. In this trial, a single, simple, home-based exercise is applied, thus, investigating whether an alternative exercise treatment, which is simplified and maintained unsupervised at home, might be offered to these patients.

This trial protocol follows the Standard Protocol Items: Recommendations for Interventional Trials (SPIRIT) Checklist (Fig. 2, Additional file 1) [24] and the exercise intervention is reported according to the TIDieR Checklist (Additional file 2) [26] allowing for replication and direct clinical use, which has been requested in a recent review [53]. The cross-sectional design mimics everyday practice of cross-sector boarder communication increasing the external validity for future clinical implementation.

### Limitations

The trial has some limitations which must be taken into consideration. There is no control group limiting the inferences that can be made on the effect of the knee-extensor strength exercise.

Due to the nature of the intervention (exercise) there is a risk of selection bias, e.g., patients motivated for exercise are more likely to participate in the trial. This also limits the external validity with respect the whole knee OA population.

In the present trial design, the patients are asked about their *need for surgery* after the 12-week exercise period. In line with the above limitation, the answer to this question could be biased as patients motivated for exercise might be less motivated towards surgery affecting their answer to *need for surgery* towards.

Though the sensor objectively measures activity with the elastic exercise band, the sensor cannot measure who is exercising, which muscle is exercised or what movement is performed.

Finally, no recording or monitoring of the use of knee-related pain medication during the trial is planned for.

## Trial status

Protocol version no. 4.1 (21 November 2017). Inclusion began 1 November 2016. Approximate date for inclusion completion is 31 December 2019.

## Abbreviations

6MWT: 6-Minute Walking Test
ASA: American Society of Anesthesiologists’ physical status classification
ICC: Intraclass correlation coefficient
ITT: Intention-to-treat
KOOS: Knee Osteoarthritis Outcome Score
MDC: Minimal detectable change
Nm/kg: Newton-meter (torque) per kilogram body mass
NRS: Numeric Rating Scale
OA: Osteoarthritis
OKS: Oxford Knee Score
RM: Repetitions-maximum
SCT: Stair Climb Test
SEM: Standard error of measurement
TKA: Total knee arthroplasty
TUT: Time-under-tension
